## Abstract

**Clinical trial registration:**

https://clinicaltrials.gov/study/, identifier NCT06931730.

## Introduction

1

Obesity is a complex chronic and relapsing disease caused by a combination of genetic, epigenetic, psychological, behavioural, social and environmental factors (1). According to the World Obesity Atlas 2024 report (2), the prevalence of childhood obesity has increased significantly over the recent years, with metabolic abnormalities already detectable in preschoolers at the onset of overweight (3). The prolonged COVID-19 lockdown, that has forced people to sedentary lifestyle, has negatively impacted health, leading to an increase in the prevalence of overweight and obesity, especially in youngers (4).

Children and adolescents with obesity are at an increased risk of experiencing depression, anxiety, social isolation, and impairments in self-esteem, self-efficacy, and quality of life (5–8), as well as sleep disorders (9). Additionally, cognitive deficits have been documented in this population (10), including impairments in long-term memory (11), executive functions (12), and attentional processes (13).

These negative effects appear to persist into adulthood, contributing to impaired synaptic plasticity and increasing vulnerability to age-related cognitive decline (14–16). Indeed, obesity is associated with brain alterations that affect individuals across the lifespan, from childhood to older adulthood (17). Among these, hippocampal abnormalities have been observed already in children with obesity (18). Hippocampal dysfunction may interfere with weight loss treatment (15) by weakening the ability to recall inhibitory associations tied to satiety signals (19). As a result, individuals may fail to regulate food intake effectively, responding instead to external food cues.

Leptin is a hormone that regulates appetite and energy expenditure by influencing energy homeostasis and satiety signalling. Leptin receptors are widely distributed in various brain structures, including the hippocampus, where leptin influences learning and memory processes (20, 21). Thus, leptin is involved in hippocampal long-term potentiation (22), long-term depression, and motivational eating (23). In individuals with obesity increased leptin secretion lead to leptin resistance, which represent a significant barrier to successful weight loss (15). Therefore, leptin resistance might be considered the molecular bridge between metabolic dysregulation and cognitive dysfunctions due to hippocampal abnormalities, particularly memory, often seen in obesity (24). In children, obesity-induced hyperleptinemia and leptin resistance may have an even greater impact on synaptic plasticity of their developing brain, contributing to emotional and behavioural dysfunctions (7) and cognitive deficits (10).

Current treatment strategies for overweight and obesity primarily focus on dietary modifications and Physical Activity (PA), both of which reduce body mass index (BMI) and improve metabolic parameters, including lipid profiles and blood sugar levels (25). However, given the multifactorial and complex nature of overweight and obesity, interventions (26) targeting cognitive abilities and social relationship - often reduced in individuals with excess weight—could provide significant benefits.

Cognitive Training (CT) may support early modulation of synaptic plasticity by mitigating leptin resistance, potentially contributing to weight loss. In animal models, the enhancement of cognitive and social stimulation, along with PA opportunities and sensorimotor stimulation, is encompassed within what is referred to as an enriched environment – EE (27). Specifically, studies in rodents have highlighted a significantly positive and protective effect of EE, influencing hippocampal neurogenesis as well (28). Moreover, while PA alone can partly restore leptin sensitivity (29), the enhancement of cognitive, sensory and social stimulation further increases leptin response, and causes a synaptic reorganization in hypothalamic feeding circuits (30). In a high-fat, high-cholesterol rat model, beneficial effects on cognition have been observed, alongside changes in gut microbiota composition. This suggests that energy homeostasis, cognition, and the microbiota are interconnected through the gut-brain axis (31). Additionally, in laboratory rodents, EE induces neural plasticity in brain regions responsible for metabolic homeostasis and cognitive function (32, 33), especially in early postnatal stages (30).

These findings suggest that comprehensive interventions, including cognitive and social stimulation, could be more effective in addressing obesity-related metabolic and cognitive dysfunctions, particularly in children and adolescents; however, evidence in humans remain limited (34, 35).

In summary, while traditional overweight and obesity intervention focus on diet and PA, multi-component interventions focusing on EE, which involve CT and Social Training (ST) may provide additional benefits by improving leptin sensitivity and enhancing neural plasticity.

This may be especially true in early childhood, which represents a critical time window to boost leptin sensitivity and reprogram the energy balance set point through appropriate protocols reproducing EE.

## Hypothesis and aims of the resilient project

2

The present project hypothesizes that the combination of ST and CT with Intensive Health Behavior Treatment (IHBT; 26), which includes PA and dietary interventions, will lead to an improvement in leptin sensitivity in children following treatment for overweight and obesity.

Since direct assessment methods used in animal models are not feasible in humans, this study will rely on alternative proxies previously used to evaluate leptin sensitivity. In humans, except for rare pathological conditions such as congenital leptin deficiency or lipodystrophy, leptin administration is not approved. In rodent models, leptin sensitivity is typically assessed through a more direct and rigorous procedure. This involves administering recombinant leptin, followed by measuring food intake and/or evaluating leptin signalling in the brain. The latter is achieved by analysing the activation of intracellular effectors, such as STAT3 and Extracellular signal-regulated protein kinases 1 and 2 (ERK1/2), after hypothalamic dissection.

In our participants, we will estimate leptin anorectic effect by calculating the ratio between circulating leptin levels and total calorie intake measured during an ad libitum laboratory meal. This ratio will serve as the primary outcome to assess changes in leptin sensitivity. Additionally, molecular analysis will be conducted on Peripheral Blood Mononuclear Cells (PBMCs) to monitor the activation of leptin signalling pathways, as previously performed in other human studies (36).

As a secondary outcome, we will explore the association between changes in leptin sensitivity and improvements in cognitive measures, such as spatial and verbal long-term memory and spatial and verbal working memory.

Additionally, some supplementary endpoints will be measured at each time point to provide a more comprehensive understanding of the intervention’s effects.

## Materials and methods

3

### Study design

3.1

To test the hypothesis, we designed an 8-week randomized clinical trial (RCT) involving children aged 6 to 11 years with overweight or obesity. The choice to conduct an 8-week intervention was based on several considerations. Firstly, extending the intervention beyond this timeframe would likely reduce long-term participants compliance. Secondly, longer interventions require greater financial and personnel resources, making them less feasible in a clinical research context. Finally, although conducted in a murine model, the study the study by Mainardi and colleagues (30) demonstrated that relevant effects at the cellular and molecular levels are already observable after a similar duration, supporting the translational validity of our timeframe. Participants will be allocated to 1 of 3 groups: IHBT group, CT+IHBT group, and ST+IHBT group. After the intervention phase, all treatments will be suspended for a 12-week wash-out period to evaluate the persistence of effects on both primary and secondary outcomes. **Figure 1** summarizes the study design and RESILIENT project timeline.

**Figure 1 f1:**
[figure not shown]
Study design and RESILIENT project timeline, showing the interventions types and intervention effects.

### Participants

3.2

A total of 120 children with overweight or obesity, referred to the Unit of Endocrinology and Diabetology of the Bambino Gesù Children’s Hospital in Rome, will be consecutively recruited during daily clinical activities by a team of highly trained endocrinologists and nutritionists and randomized to treatment. Parents or legal guardians will receive comprehensive instructions regarding the procedures and objectives of the experiment. Clinicians will obtain written consent and assent from the participating child before enrolment in the study. Participation will be solely voluntary.

No financial compensation or reward will be provided for participants.

Inclusion criteria are the followings: a) age 6 to 11 years-old; b) a condition of overweight and obesity defined as follows: *“overweight”* defined as BMI ≥ 85th percentile (1.036 SD) and < 95th percentile (1.645 SD) percentiles, *“obesity”* as a value of BMI ≥ 95th percentile (1.645 SD); and *“severe obesity”* as a value of BMI ≥ 120% of the 95th percentile (2.326 SD), based on CDC reference charts (37); d) an Intelligence Quotient (IQ) higher or equal to 85 (IQ ≥ 85); c) possession of electronic devices such as a computer or tablet.

Exclusion criteria include the presence of: a) genetic or syndromic obesity; b) reduced mobility; c) systemic diseases; d) ongoing pharmacological treatment for chronic conditions.

### Trial arm allocation

3.3

Participants will be randomized into 3 8-week trainings as follows: a) IHBT group (n = 40); b) CT+IHBT group (n = 40) or c) ST+IHBT group (n = 40).

Randomization will be performed according to a block-randomization list, stratified by gender and age (6–11 years), and generated using the ralloc routine in STATA 17 software before enrolment.

### Sample size

3.4

The sample size for the 3-arm study was determined considering the different decrease of leptin values (an indirect estimate of the primary endpoint leptin sensitivity), following the intervention (mean values of 10 mg/dL in the IHBT group compared to 6 mg/dL in the ST+IHBT or CT+IHBT group, SD = 4). An effect size of 1 was considered as clinically relevant (comparing CT+IHBT group vs. IHBT group and ST+IHBT group vs. IHBT group using Student’s t-test).

Pairwise comparisons will be performed with a significance threshold of p < 0.017 to account for multiple comparisons (3 comparisons), using Bonferroni corrections (p = 0.05/3). To achieve a significance level of alpha equal to 0.017 and a study power of 95%, 30 patients per group are required; considering a 30% dropout rate during follow-up, the plan is to recruit a total of 120 participants (40 per group). Missing data will be excluded from the statistical analyses; otherwise, if the proportion of missing values does not exceed 20%, we will use a mean substitution method, or a multiple imputation method (as for example KNN) as needed.

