### Study assessments

3.6

Outcome variables for all participants will be assessed at baseline (T0), at the end of the 8-week intervention (T1, end of month 2), and 12 weeks after the intervention (T2, end of month 5) to verify the persistence of effects. During the intervention period (T0-T1), participants will receive 3 online nutritional counselling sessions, each conducted every 15 days. Additionally, 2 online follow-up sessions (between T1-T2) are scheduled to occur once per month with nutritionists and PA trainer to support adherence to dietary guidelines, monitor progress, and provide ongoing support.

**Figure 2** provides a detailed overview of the assessment and procedural steps involved in the study protocol across all phases of the research. Further details regarding the specific measures and evaluations conducted at each stage of the study will be extensively described in the subsequent sections of the manuscript.

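### The only between-arm test the article names is Student's t-test, with no adjustment for the T0 value, gender or age, although all three are collected

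*Protocol article*

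**What the plan says.** Protocol article, Sample size (3.4): the effect size is explained by "comparing CT+IHBT group vs. IHBT group and ST+IHBT group vs. IHBT group using" Student's t-test. The section then turns to the analysis: "Pairwise comparisons will be performed with a significance threshold of p < 0.017 to account for multiple comparisons (3 comparisons"). It also sets rules for missing data, so it is the nearest thing the article has to an analysis section. The sizing inputs are a decrease in leptin, with "mean values of 10 mg/dL in the IHBT group compared to 6 mg/dL in the ST+IHBT or CT+IHBT group, SD = 4", and "An effect size of 1 was considered as clinically relevant".

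Trial arm allocation (3.3): block randomisation, "stratified by gender and age".

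Study assessments (3.6): "Outcome variables for all participants will be assessed at baseline (T0") and again at T1 and T2. The leptin sensitivity section (3.6.6.1) confirms that the fasting leptin sample for the primary index is drawn at all three visits.

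No covariate is mentioned for the primary outcome. The article does consider a covariate elsewhere: lymphocyte percentage, for the ex vivo cell-signalling data (3.6.6.2).

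**The concern.** Eligible children run from overweight to severe obesity and from 6 to 11 years of age. Leptin and meal intake will probably differ widely between them, and the T0 measurement should explain part of that spread. BMI category is not a stratification factor, so a T1 comparison would also carry any chance imbalance in baseline adiposity or leptin.

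Stratifying on gender and age balances those factors between arms. A t-test that ignores them leaves the variation they explain in its standard error. If they predict the outcome, that standard error is too large for the design and the test is conservative.

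What is at stake is precision, in a trial expecting about 28 completers per arm and testing at 0.017. Validity is not at stake.

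**Working it through.** **Inputs from section 3.4.** Difference 10 − 6 = 4; SD 4; effect size d = 4/4 = 1; alpha 0.017 per comparison; stated power 95% with 30 per group; 40 recruited per group; dropout 30%. Sidedness is not stated. The T0–T1 correlation rho is not given, so it is varied.

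**The plan's own figure.** Power comes from the noncentral t distribution with 2n − 2 degrees of freedom and noncentrality d × √(n/2).
- One-sided alpha 0.017: n = 30 gives 95.3%, which reproduces the stated 30.
- Two-sided alpha 0.017: 34 per group are needed (33 by the normal approximation), and n = 30 gives 91.8%.
- Completers after the stated dropout: 40 × 0.7 = 28. Power is then 89.5% two-sided, or 93.9% one-sided. Retaining 30 would need 30/0.7 = 42.9, so 43 recruited per group.

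The comparison below uses 28 per arm and a two-sided test, so its starting point is 89.5%.

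**Reading A: SD 4 is the SD of the T1 value.** Adjusting for T0 multiplies the residual variance by 1 − rho². The effective effect size becomes d/√(1 − rho²), with 2n − 3 = 53 degrees of freedom. At rho 0.5, for example, it is 1/√0.75 = 1.155.

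| rho (assumed) | variance factor | power, 28 per arm |
|---|---|---|
| 0 | 1.00 | 89.5% |
| 0.2 | 0.96 | 90.8% |
| 0.3 | 0.91 | 92.4% |
| 0.5 | 0.75 | 96.5% |
| 0.6 | 0.64 | 98.5% |
| 0.7 | 0.51 | 99.7% |

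Power reaches 95% once rho is at least about 0.43.

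**Reading B: SD 4 is the SD of the change.** With a common SD s at both visits, a change score has variance 2s²(1 − rho) and ANCOVA has s²(1 − rho²). The ratio is (1 + rho)/2, which is below 1 for any rho below 1.

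| rho (assumed) | variance factor | power, 28 per arm |
|---|---|---|
| 0.5 | 0.75 | 96.5% |
| 0.6 | 0.80 | 95.4% |
| 0.7 | 0.85 | 94.1% |
| 0.8 | 0.90 | 92.7% |
| 0.9 | 0.95 | 91.1% |

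Here power reaches 95% only if rho is at most about 0.63.

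**Confidence interval width** scales with the square root of the variance factor. Under reading A it shrinks by about 2% at rho 0.2 (√0.96 = 0.98), 13% at 0.5 (√0.75 = 0.87) and 29% at 0.7 (√0.51 = 0.71). Under reading B it shrinks by 13% at rho 0.5 and about 3% at 0.9 (√0.95 = 0.97).

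**Cost of adjusting.** If T0 were useless (rho = 0), losing one degree of freedom moves power from 89.53% to 89.50%. The further gain from gender and age cannot be computed, because the article does not say how strongly they predict the outcome.

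**The case against.** Four points can be made on the other side.

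1. **The t-test sits in a sizing parenthesis.** Sizing on a simple test and adjusting in the analysis is common, and a SAP that is not shown may do so. This stands as a limit: a reader might infer that the final primary analysis is fixed as an unadjusted t-test, and the article does not go that far. What remains is that it is the only between-arm test named, in a section that goes on to say how the pairwise comparisons will be performed and how missing data will be handled.

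2. **Baseline may already be used.** The sizing speaks of a decrease in leptin, and section 2 describes the primary outcome as assessing changes in leptin sensitivity. A t-test on change would use T0. So one cannot say that T0 is ignored altogether. But a change score fixes the baseline slope at 1, and reading B shows that ANCOVA still has the smaller variance.

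3. **The power shortfall has other causes.** It comes from the unstated sidedness and from the dropout inflation, not from the choice of test. On a one-sided reading, 30 per group already gives 95.3%. This stands: adjustment does not correct those figures.

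4. **The numbers are for leptin, not for the primary index.** The index is a ratio of meal intake and leptin. The article gives no SD, effect size or correlation for it, and meal-to-meal variation could lower rho. This also stands, so the figures show direction and possible size only.

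Randomisation also keeps the unadjusted comparison unbiased in expectation, and ignoring the strata errs on the conservative side. A charge of invalidity would not hold.

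**Conclusion.** The point holds as a matter of efficiency. The one between-arm test named adjusts for none of T0, gender and age, all of which are collected, and an adjusted model would generally be more precise on either reading of SD 4. On the sizing variable at 28 per arm, two-sided, adjustment lifts power from 89.5% to between 90.8% and 99.7% (reading A, rho 0.2–0.7), or to between 96.5% and 91.1% (reading B, rho 0.5–0.9).

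A reader might conclude that adjustment would restore the stated 95%. The article does not support that. It gives no rho, and the result fails below about 0.43 on reading A and above about 0.63 on reading B.

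The conclusion rests on an assumed rho, a two-sided test, 30% loss in every arm and, for reading B, equal SDs at T0 and T1. The direction of the gain is firm; its size is not. This should be changed, but it does not invalidate the design.

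**What to change.** Add one sentence on the primary analysis: the pairwise comparisons at T1 will be estimated from a single ANCOVA (or an equivalent repeated-measures model) of the primary leptin-sensitivity index, with arm, T0 index, gender and age (as used for stratification) as covariates. A log scale for the index and baseline fat mass from bioimpedance are optional additions. If a SAP already specifies such a model, align section 3.4 with it.

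Any power claimed for the adjusted analysis should be given with the assumed rho and its range, and with a statement of whether SD 4 refers to the T1 value or to the change. Sidedness and the dropout inflation still need correcting separately.

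The cost is one sentence and no new data. The covariates take a few degrees of freedom: one each for T0 and gender, and one or more for age, depending on how it was banded. Fitting all three arms in one model offsets this if the residual variance is common. With one degree of freedom per covariate, 3 × 28 − 3 arms − 3 covariates = 78 remain, against 2 × 28 − 2 = 54 for a two-arm t-test.

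### Testing all three pairs at a fixed Bonferroni 0.017 is valid but needlessly conservative; a three-arm closed (Shaffer) rule recovers power for a change of wording

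*Protocol article*

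**What the plan says.** Section 3.4 (Sample size) sets one threshold for every pair of arms: "Pairwise comparisons will be performed with a significance threshold of p < 0.017 to account for multiple comparisons (3 comparisons), using Bonferroni corrections", that is, 0.05/3. The planning values in the same section are "mean values of 10 mg/dL in the IHBT group compared to 6 mg/dL in the ST+IHBT or CT+IHBT group, SD = 4". The effect size is attached to two of the three pairs: "An effect size of 1 was considered as clinically relevant (comparing CT+IHBT group vs. IHBT group and ST+IHBT group vs. IHBT group using Student’s t-test". The size then follows: "To achieve a significance level of alpha equal to 0.017 and a study power of 95%, 30 patients per group are required". Recruitment is set at 40 per group to allow for 30% dropout.

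No step-down or closed procedure is mentioned. The section does not say whether the tests are one- or two-sided, and it does not say that both add-ons must beat IHBT for the trial to succeed. The Discussion says the trial will separate the contributions of CT, ST and PA, which is what the third pair, CT+IHBT against ST+IHBT, addresses.

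**The concern.** A fixed Bonferroni threshold treats the three pairwise nulls as if any combination of them could be true. With three arms that is not so: if two of the pairs are equal, the third must be equal as well. A threshold of 0.017 on every test therefore guards against situations that cannot occur.

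What is at stake is power. The trial's hypothesis concerns cognitive training and social training alike, so an answer on each add-on is wanted. Each child attends two days of testing at each of three time points, so power that costs no extra children is worth having.

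**Working it through.** **Inputs (section 3.4).** Means 10 (IHBT), 6 (CT+IHBT), 6 (ST+IHBT); SD 4. Standardised difference for each add-on against IHBT: (10 − 6)/4 = 1. For CT+IHBT against ST+IHBT: (6 − 6)/4 = 0. Evaluable children per arm: the stated 30, and 40 × 0.70 = 28 after the stated dropout. Sidedness is not given; I take two-sided as the main case and show one-sided as the range.

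**Step 1: reproduce the stated 30 per group.** Normal approximation, n = 2(z_α + z_0.95)²/d².
- One-sided 0.017: 2 × (2.120 + 1.645)² = 28.4, so 29. With the t distribution, 29.5, so 30. This matches the document.
- Two-sided 0.017: 2 × (2.387 + 1.645)² = 32.5, so 33. With the t distribution, 34. At 30 per group, two-sided power per comparison is 91.8%.

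**Step 2: why the other two tests can be run at 0.05.** Let H1 be CT+IHBT = IHBT, H2 be ST+IHBT = IHBT, and H3 be CT+IHBT = ST+IHBT. Any two of these imply the third, so every intersection of two or more is the global null. A closed test then needs only (a) a level-0.05 test of the global null, here smallest p ≤ 0.05/3, and (b) each pair at 0.05.
- All three nulls true: an error requires rejecting the global null, probability at most 5%.
- Exactly one null true: an error requires that pair to have p ≤ 0.05, probability at most 5%.
- Exactly two true: impossible.

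Any pair rejected at 0.05/3 by the fixed rule is also rejected by the closed rule. The only exception comes from rounding 0.05/3 = 0.0167 up to 0.017.

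**Step 3: power.** Simulation of three normal arms at the planning values, pairwise two-sided t-tests:

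| Power to show | 30/arm, fixed 0.017 | 30/arm, closed | 28/arm, fixed 0.017 | 28/arm, closed |
|---|---|---|---|---|
| both add-ons superior | 86.0% | 93.5% | 82.5% | 91.4% |
| a given add-on superior | 91.8% | 95.5% | 89.5% | 94% |
| at least one add-on superior | 97.5% | 97.5% | 96.5% | 96.5% |

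- Gain for both add-ons: 93.5 − 86.0 = 7.5 points at 30 per arm; 91.4 − 82.5 = 8.9 points at 28.
- Ordinary Holm over three gives 89.6% at 30 per arm, a gain of 3.6 of the 7.5 points, or about half.
- One-sided add-on tests at 30 per arm: 91.8% to 96.9%, a gain of 5.1 points.
- The fixed threshold would need about 36 to 37 evaluable children per arm (93.2% and 94.0%) to match what the closed rule gives at 30.
- If only one add-on works (means 10, 6, 10; 30 per arm), power to show that it beats IHBT rises from 91.8% to 95.5%.

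**Step 4: error rates, 30 per arm.** All arms equal: family-wise error about 4.4% under either rule. One true null, with the other two pairs different: 1.7% under the fixed rule, 5.0% under the closed rule.

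**The case against.** The strongest reply is that nothing here is wrong. Single-step Bonferroni is valid, was specified in advance, and is the level at which the trial was sized. The document never requires both add-ons to win, and the gain is largest on that criterion. Per comparison it is about 4 points, on a one-sided reading about 5 points for both add-ons, and for at least one add-on there is none. All figures are for leptin, which the section itself calls an indirect estimate of the primary endpoint, so none is power for the ratio of calories to leptin. All of this stands. It makes the point an efficiency gain rather than a fault, but it does not remove the gain.

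A reader might infer three stronger things that the document does not support.

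- **That CT+IHBT against ST+IHBT wastes alpha and should be demoted.** The equal planning means show only that the trial was not sized on that contrast. It serves a stated aim, and the closed rule keeps it confirmatory.
- **That testing at both T1 and T2 breaks the 5% level.** The 12-week wash-out is there "to evaluate the persistence of effects on both primary and secondary outcomes", and sizing rests on values following the intervention. Nothing makes T2 a second confirmatory test at 0.017, and naming the confirmatory time point is commonly left to the analysis plan.
- **That the change is free.** Family-wise error is held, but a single true null is tested at 5% instead of 1.7%. For example, if both add-ons work equally, a false claim that they differ becomes about three times as likely. Simple simultaneous confidence intervals that match the tests are lost.

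**Conclusion.** This is a cheap improvement, not an error. The fixed 0.017 threshold gives up about 7.5 points of power to show both add-ons superior at 30 per arm and about 9 points at 28, and about 4 points for each add-on. The closed rule recovers these with family-wise error still at or below 5%.

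The figures assume the planned effect size of 1 on leptin, normal data with SD 4, equal arms and two-sided tests. The closure argument itself needs none of these. It rests only on there being three arms and three pairwise equality nulls, with each test valid at its level.

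**What to change.** In section 3.4, replace the fixed threshold by wording such as: the three pairwise comparisons are tested by a closed step-down procedure in Shaffer form; the smallest of the three p-values is compared with 0.05/3, and if it is significant each of the other two comparisons is tested at 0.05; otherwise none is declared significant. Name the Shaffer form, because a sponsor who adopts ordinary Holm (0.05/3, then 0.05/2, then 0.05) keeps only about half the gain. Use 0.05/3 itself, not the rounded 0.017. Keep all three comparisons in the family.

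The cost is one sentence, and no extra children. The sponsor accepts a 5% rather than 1.7% error rate for a single true null, and the plan should say that reported confidence intervals will not be simultaneous intervals matching the tests. Make the change before any unblinded outcome data are seen.

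### 40 per group does not absorb the planned 30% dropout: 28 remain, not 30, and power is 89.5% (two-sided) or 93.9% (one-sided), not 95%

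*Protocol article*

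**What the plan says.** All the inputs are in section 3.4 (Sample size) of the protocol article.

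- **Effect:** "mean values of 10 mg/dL in the IHBT group compared to 6 mg/dL in the ST+IHBT or CT+IHBT group, SD = 4". The section adds: "An effect size of 1 was considered as clinically relevant".
- **Test:** Student's t-test of each combined arm against IHBT.
- **Significance level:** "Pairwise comparisons will be performed with a significance threshold of p < 0.017 to account for multiple comparisons (3 comparisons", obtained as 0.05/3. The section does not say whether the test is one- or two-sided.
- **Result and dropout allowance:** "a study power of 95%, 30 patients per group are required; considering a 30% dropout rate during follow-up", followed by "the plan is to recruit a total of 120 participants (40 per group").
- **Variable:** leptin, described as "an indirect estimate of the primary endpoint leptin sensitivity".
- **Missing data:** to be excluded, with imputation allowed only where no more than 20% of values are missing.

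**The concern.** Two steps need checking: from the design assumptions to 30 evaluable per group, and from 30 evaluable to 40 recruited. This is the only sample-size justification in the article. If the second step is wrong, the trial does not reach its stated power once the dropout it plans for has occurred. If the first step depends on an unstated choice of sidedness, a reader cannot tell what 95% refers to. The missing-data rule does not close the gap: at 30% missing, the 20% limit on imputation is exceeded, so the analysis falls back on complete cases.

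**Working it through.** **Inputs** (all from section 3.4): difference 10 − 6 = 4, SD 4, so d = 4/4 = 1; alpha 0.017 per comparison; power 95%; dropout 30%; 40 recruited per group. Sidedness is not given, so both readings are computed.

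**Step 1: the stated 30 per group.** For a two-sample t-test with n per group, power comes from the noncentral t distribution with 2n − 2 degrees of freedom and noncentrality d × √(n/2). The critical value is at 1 − 0.017/2 (two-sided) or 1 − 0.017 (one-sided).

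| Evaluable per group | Power, two-sided 0.017 | Power, one-sided 0.017 |
|---|---|---|
| 28 | 89.5% | 93.9% |
| 30 | 91.8% | 95.3% |
| 40 | 97.7% | 98.9% |
| Smallest n for 95% | 34 | 30 |

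The plan's figure of 30 is therefore reproduced exactly by a one-sided test and not by a two-sided one. The normal approximation agrees: two-sided, 2 × (z₀.₉₉₁₅ + z₀.₉₅)² / d² = 32.5, so 33 per group; one-sided, it gives 29. Using exactly 0.05/3 in place of 0.017 changes little: 35 two-sided and 30 one-sided.

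**Step 2: from 30 evaluable to 40 recruited.** To have n evaluable after a proportion q is lost, recruit n/(1 − q).

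- Needed for 30 evaluable: 30/0.70 = 42.9, so 43 per group and 129 in total.
- Left from 40: 40 × 0.70 = 28.
- Loss that 40 can absorb while keeping 30: 1 − 30/40 = 25%.
- Multiplying instead of dividing gives 30 × 1.3 = 39. This is close to 40 and may be how the figure arose.

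This step does not depend on sidedness. Starting from 34 would only widen the gap: 34/0.70 = 48.6, so 49 per group and 147 in total.

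**Step 3: power after the planned loss.** At 28 per group, the chance of missing a true effect of 1 SD in one comparison is 100 − 89.5 = 10.5% two-sided, or 100 − 93.9 = 6.1% one-sided. The stated 95% power implies 5%.

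**Step 4: if less than 30% is lost by T1.** Two-sided power at 34 evaluable is 95.0%, which corresponds to a loss of 6/40 = 15%. One-sided power is at least 95% down to 30 evaluable, a loss of 10/40 = 25%.

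**The case against.** **Sidedness.** A reader might infer that 30 per group is simply wrong and that 34 are needed. The article does not support that. It never states the sidedness, and a one-sided t-test at 0.017 gives 30. A three-group F-test at 0.017 also gives 30 (95.1% power), although the article names the t-test. In favour of the two-sided reading, it is the usual convention, and the threshold covers three pairwise comparisons, including CT+IHBT against ST+IHBT, for which section 2 and the Discussion state no direction. That makes two-sided the more natural reading but does not establish it. What stands is that the starting figure is ambiguous.

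**Timing of dropout.** The 30% is described as loss during follow-up. Section 3.6 and the Figure 2 legend use that term for the period after T1 and for T2. If part of the loss occurs only then, more than 28 per group remain at T1. This is a fair point: 28 is the figure after the whole planned loss and is not necessarily the number at T1.

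**The surrogate.** A reader might also infer a specific, larger loss of power for the primary ratio of leptin and meal intake. The article gives no variance for intake, so any such number would rest on assumed inputs. It also says openly that leptin is an indirect estimate. What stands is only that the stated power does not describe the primary endpoint.

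**Importance.** Power of roughly 90% or more for a 1 SD effect is still good, and no test or error rate is invalidated. This limits the severity; it does not make the stated figure correct.

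**Conclusion.** Wrong as written, of moderate severity. The dropout step fails on every reading: 40 per group with 30% loss leaves 28, two short of the plan's own requirement, and 40 covers 25%. With 28 evaluable, power per comparison is 89.5% two-sided or 93.9% one-sided; neither is 95%. The claim that 30 evaluable give 95% power holds only for a one-sided test, which the article does not specify; two-sided it is 91.8%.

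These figures assume d = 1, equal group sizes, the t-test named in section 3.4, alpha 0.017, complete-case analysis and the full 30% loss. Power at T1 is higher if some of that loss falls after T1. The finding does not show that the trial is unviable or that more children must be recruited.

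**What to change.** Keep 120 participants and correct the text of section 3.4:

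1. State whether the 0.017 threshold is one- or two-sided.
2. Restate the power in one of two ways. Either: '40 randomised per group, 28 evaluable after 30% dropout, give 89.5% power per pairwise comparison (effect size 1, two-sided alpha 0.017)'. Or: say that 40 per group covers 25% dropout, with 91.8% two-sided power at 30 evaluable. If the test is one-sided, the corresponding figures are 93.9% at 28 and 95.3% at 30.
3. Say whether the 30% loss is expected by T1 or by T2.
4. Add that this power is for leptin as a surrogate and not for the primary ratio of leptin and meal intake.

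The cost is a text correction and a slightly less favourable stated power. Recruitment, allocation and assessments do not change.
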